### Interventions

#### Intervention group

Participants in the intervention group will be provided with a multi-factorial, integrated approach which incorporates both standardised and responsive components. At the point of discharge from inpatient rehabilitation, the participants will receive:

1) written material developed by the National Stroke Foundation relating to recovery after the event of a stroke (Booklet: *Long Term Recovery*, and seven Factsheets: *Movement and exercise after stroke, Depression after stroke, Medication after stroke, Communication after stroke, Sexuality after stroke, Diet after stroke, Thinking and perception after stroke*) [42].

2) written stroke information resources, including contact phone numbers (and websites, if available) for: The National Stroke Foundation, The Stroke Association of Victoria, Brain Foundation of Victoria, Headway Victoria, the participant's local Municipal Council, and a local stroke support group (if available). The participants will also receive the contact details of the inpatient Rehabilitation Unit and the project research co-ordinator. Carer participants will be given the contact details of: Carers Victoria (including the Carer Counselling Service, and Commonwealth Carer Resource Centre Victoria), Commonwealth Carer Respite Centre, and local carer support groups (if available).

3) a copy of the goals that were collaborately devised by the participant and the rehabilitation team during the final two weeks of the inpatient rehabilitation admission

In addition to the above interventions,

4) written correspondence will be sent (at the point of inpatient rehabilitation discharge) to the General Practitioner outlining the participant's involvement in the study, the aim of the study, and a copy of the collaborative goals.

5) written correspondence will also be sent to the main community-based rehabilitation services that the patient has been referred to for ongoing management (such as Community Rehabilitation Centre, Rehabilitation in the Home or other domiciliary-based services).

6) phone contact will be made with participants at two and six weeks post-discharge. The nature of these contacts is to enquire about:

- current participant activity status (for example, *How are you currently managing being at home? How are you managing with your everyday activities? *Verify which post-discharge services are in place).

- how the participant is progressing with their goals (including identification of barriers, and discussion regarding possible solutions).

- any falls, accidents, medical issues arising, or injuries sustained.

- mood status (for example, *How are you feeling? Is there anything that is worrying you? Are there any concerns or needs that you feel are currently not being addressed?*).

- presence or absence of informal supports (such as family, friends, and community-based supports). Determine what type of support is being offered (for example, emotional support and/or practical support).

- whether the participant is interested in attending a stroke support group (if one is available in the local area).

7) Home visit to participant's residence at three months post-discharge. The enquiries made during this visit follow a similar format as the previous phone contacts. It is considered by the researchers that this informal 'face-to-face' visitation is a key component, as it takes place in the patient's context. This may allow for a better overview and evaluation of the patient's abilities through actual visualisation of their current activity status. In addition, environmental factors (within the home and immediate community) and carer/family interactions can be gauged. During the home visit, emphasis will also given to the 'best effort' that the participant has achieved to date regarding their activity and participation status. Verbal encouragement will be given to maintain or increase the frequency or achievement level of their activity status, as appropriate. At this three month timepoint, enquiries will also be made as to the patient's perception of the utility of the written material that was received at discharge (Booklet and Factsheets). The participants will be asked whether they have read the written material, and whether or not they considered the information to have been useful.

8) Interventions determined on a 'needs' basis, to facilitate goal achievement and community re-integration.

9) Review of assessment findings at 6 months, and implement interventions in response to the obtained data.

10) Telephone contact at nine months post-stroke to re-evaluate status and initiate any additional interventions, as required.

All the standardised intervention components (listed above as numbers 1-10) will be conducted by the primary researcher, who is a senior physiotherapist experienced in neurological rehabilitation, and not involved in the assessments. Should additional interventions be required, referrals will be made to relevant healthcare resources with correspondence outlining the arising issue and a request for appropriate assessment and management (for example: assessment of community access options with consideration of utilising an electric scooter to enable greater outdoor distances; review of urinary incontinence by the catchment Continence clinic; request for the general practitioner to assess and manage a patient's evolving low mood).

Verbal support will be given to the participants and their carers at all contacts, including acknowledgement of achievements to date and encouragement to continue to pursue activities and goals. Verbal support will also particularly be offered to those participants who display evidence of low mood status. Intervention group participants will continue to receive usual care from health and community resources as deemed appropriate by their medical consultants and treating team. The telephone details for the researcher will be given to the participant at each contact point, with the recommendation to make contact with the researcher if they have any queries or concerns about their recovery post-stroke.

During the phone contacts and home visit, issues or 'flags' may emerge that give rise to the need for additional interventions. Table 1 outlines the guidelines for interventions in response to certain 'flags'. However, as the interventions are based on the arising needs of an individual participant, the interventions listed in Table 1 are not exhaustive, but rather a strategy for initial clinical decision making. 'Flags' may also be discerned during scrutiny of the outcome data that is collected at the blind assessments conducted at six months post-stroke. Some of the intervention options may not need to be exercised, as the current treating team may already be aware of the issues and be providing the relevant service.

**Table 1 T1:** Guidelines for interventions based on arising 'flags'

Domain	'Flags'	Intervention options
Post-discharge services	- The services organised at discharge from inpatient rehabilitation have not commenced as scheduled	- Contact relevant service to determine referral status - Liaise with inpatient rehabilitation clinicians to verify referral status

Activity status	- Decline in activity status/functional decline (including PADL, mobility, continence) - Failure to progress in activity status in valued activities	- If participant is currently attending community-based rehabilitation services, liaise with relevant team members (such as OT/PT/SP) - If participant is not attending any community-based rehabilitation services, refer to relevant health professional for assessment and management - Inform participant about local services (such as exercise groups, hydrotherapy) as appropriate - Refer to GP for review (to exclude medical basis for decline in functional ability) - Refer to Continence Clinic, if appropriate - Refer to ACAS, if appropriate

Cognition	- Decline in cognitive function (reports from patient, family, carer) - Safety concerns due to cognitive impairments - Evidence of marked change in MMSE performance between assessment timepoints	- Refer for medical evaluation (such as GP/Rehabilitation Medicine Specialist/Geriatrician). - If participant is currently attending community-based rehabilitation services, liaise with OT regarding cognitive assessment and management - If participant is not attending any community-based rehabilitation services, refer to OT for assessment and management - Referral to Cognitive Dementia and Memory Service as appropriate

Falls	- Episodes of falls - Fear of falling limiting function	- Monitor number and nature of falls during contacts with participant. - If participant is currently attending community-based rehabilitation services, liaise with relevant team members. If team is unaware of falls, request a falls risk assessment. - If participant is not attending any community-based rehabilitation services, refer to relevant health professional for a falls risk assessment and management

Mood status	- GDS-15 score of ≥ 6 points, or marked change in GDS-15 score between assessment timepoints - Evidence during contacts of depression or mood change	- Referral to GP - Encouragement to participate in valued activities - Encouragement to participate in physical activity (as able) and enhance social contacts - Referral to CATS if urgent assessment required

Goals/Participation status	- Failure to resume, or reduced participation in, valued activities that should be achievable post-stroke - goals not being achieved based on GAS ratings at 6 & 12 month assessments	- identify barriers to goal achievement - re-establish goals as required (with regard to both timeframes and attainment level) - If participant is currently attending community-based rehabilitation services, liaise with relevant team members (such as OT/PT/SP) - If participant is not attending any community-based rehabilitation services, refer to relevant health professional who can assist with facilitating and enhancement of participation status and goal attainment

Health/Medical status	- hospital inpatient re-admission during the 12 month follow-up period	- if the researcher has knowledge of the admission, contact by phone at two weeks post-discharge to monitor status.

Informal support	- absence of informal supports that is resulting in evidence of loneliness or lack of emotional support	- Provide information to the participant about relevant local community groups/services. Facilitate referral to group/service - Provide information about closest Stroke Support Group

Carer status (for consented carer participants)	- Evidence of reduced carer coping or stress during contacts - GDS-15 score of ≥ 6 points - Zarit Burden Interview > 24 points	- Aim to identify causes of reduced coping/stress - Provide information regarding carer resources (refer to information given at inpatient rehabilitation discharge timepoint). Discuss options. - If the patient participant is currently attending community-based rehabilitation services, liaise with relevant team members (such as SW) - Encourage GP review - Offer ongoing verbal support and encouragement to the carer in their role during contacts - Continue to engage carer in the rehabilitation process

PADL: Personal activities of daily living

OT: Occupational therapist

PT: Physiotherapist

SP: Speech Pathologist

GP: General practitioner

ACAS: Aged Care Assessment Service

MMSE: Mini-mental State Examination

GDS-15: Geriatric Depression Scale (15 item)

CATS: Crisis Assessment and Treatment Service

GAS: Goal Attainment Scaling

SW: Social Worker

#### Control group

Participants in the control group will receive usual care as arranged by the treating team at the point of discharge from the inpatient rehabilitation admission. In addition, control group participants will be contacted at two and six weeks post-discharge by an experienced allied-health clinician. This study design is implemented to ensure that the participants remain blind to group allocation. No interventions or advice will be offered to the control group participants by the researchers at these timepoints. A general enquiry will be made as to whether the services that were arranged at discharge have commenced. The control group participants will only receive an intervention by the researchers if there are particular indicators of risk, such as verbal ideations of suicide/self-harm or a GDS-15 score ≥ 14.

### Power and sample size calculations

Power calculations for this study are based on nine month post stroke data (obtained six months post-intervention) for GDS-15, from a study performed by Lai et al. (2006) [43]. Based on a power of 80% and the criterion for significance set at 0.05 (two-sided), the proposed sample size is 55 participants for each arm of the study. This computation assumes that the mean difference between groups is -1.4 (corresponding to means of 2.0 versus 3.4) and the common within-group standard deviation is 2.6 (based on SD estimates of 1.8 and 3.2). Allowing for a 20% drop-out rate, the aim is to recruit 66 participants in each group, giving a total sample of 132 participants.

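### The 20% drop-out allowance multiplies 55 by 1.2 instead of dividing by 0.8, so 66 per arm leaves fewer than the 55 needed for the stated 80% power

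*Protocol article*

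**What the plan says.** The calculation is in the protocol article under Power and sample size calculations. It concerns the GDS-15 in the patients with stroke and is a plain comparison of two means. The starting figure is given as follows: "Based on a power of 80% and the criterion for significance set at 0.05 (two-sided), the proposed sample size is 55 participants for each arm". The assumed difference is 1.4 points (2.0 versus 3.4), and for the spread the article says that "the common within-group standard deviation is 2.6 (based on SD estimates of 1.8 and 3.2").

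The next step is the allowance for loss to follow-up: "Allowing for a 20% drop-out rate, the aim is to recruit 66 participants in each group, giving a total sample of 132 participants". The section shows no inflation formula and gives no other reason for 66.

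Under Statistical methods, the article names the 12-month GDS-15 total as the primary outcome. It plans mixed regression models for repeated measures, adjusted for initial FIM-motor score, history of depression, length of stay and discharge GDS-15. The sample size calculation takes no account of that adjustment.

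**The concern.** A drop-out rate is a fraction of the people recruited. To finish with a required number, that number must be divided by the fraction retained. Multiplying by one plus the drop-out rate gives too few, because the loss then acts on the enlarged total. The stated 66 is what the multiplication gives.

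If so, the four figures in the section (55 needed, 20% lost, 66 per arm, 132 in total) cannot all hold together. A trial that recruits exactly to target and loses exactly the planned fraction would end below its own stated requirement. The recruitment target and the power are headline design figures that will be repeated when the trial is reported.

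**Working it through.** **Inputs**, all from the section Power and sample size calculations: two-sided significance level 0.05; power 80%; difference 1.4; common SD 2.6, from 1.8 and 3.2; equal arms; drop-out 20%; target 66 per arm, 132 in total.

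**1. The common SD.** √((1.8² + 3.2²)/2) = √(13.48/2) = 2.596, which rounds to 2.6. It reproduces.

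**2. The 55 per arm.** Normal approximation:

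n = 2 × (1.96 + 0.8416)² × (2.6/1.4)² = 54.1, rounded up to 55.

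The two-sample t-test gives 55.1. The 55 therefore reproduces; a one-sided test would give 43 and does not.

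**3. The drop-out allowance.**

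| Quantity | Calculation | Result |
|---|---|---|
| Target by multiplication | 55 × 1.2 | 66 (as stated) |
| Target that keeps 55 | 55/0.8 = 68.75 | 69 per arm, 138 in total |
| Left after 20% loss from 66 | 66 × 0.8 | 52.8 per arm |
| Largest loss at which 66 still leaves 55 | 1 − 55/66 | 16.7% |
| Left after 20% loss from 69 | 69 × 0.8 | 55.2 per arm |

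Rounding does not explain the gap: 52.8 is below even the unrounded normal-approximation requirement of 54.1. The target is short by 69 − 66 = 3 per arm, or 138 − 132 = 6 in total.

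**4. Power on the protocol's own basis** (difference 1.4, SD 2.6, two-sided 0.05, no covariates). The normal approximation is Φ(1.4/(2.6 × √(2/n)) − 1.96). At n = 52.8 this is Φ(2.767 − 1.96) = 79.0%. The t-test column uses the noncentral t distribution.

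| Completers per arm | Normal | t-test |
|---|---|---|
| 52 | 78.4% | 77.6% |
| 52.8 | 79.0% | 78.3% |
| 53 | 79.2% | 78.4% |
| 55 | 80.6% | 79.9% |

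The loss from 55 to 52.8 is 80.6 − 79.0 = 1.6 points (normal) or 79.9 − 78.3 = 1.6 points (t-test).

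**5. What adjustment for baseline could do.** The article gives no correlation between discharge and 12-month GDS-15, so the values here are assumptions. With correlation r, the SD becomes 2.6 × √(1 − r²). At 52.8 per arm, t-test power is about 82% for r = 0.3, 85% for r = 0.4, 89% for r = 0.5 and 93% for r = 0.6. Power returns to 80% at r of about 0.16 (normal) or 0.21 (t-test).

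**The case against.** The strongest reply is that the planned analysis is not the one in the calculation. The mixed model adjusts for discharge GDS-15 and other covariates, and a correlation of only about 0.2 would bring power back to 80% at 52.8 per arm. That is a low bar for one scale measured twice. GDS-15 is also taken at six months, so in a likelihood-based model a patient lost after that visit still contributes data and is not a complete loss.

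The effect is small in any case. The t-based power at 55 is already 79.9%, so the stated 80% is itself rounded. The argument is between a 16.7% and a 20% allowance, and both are planning guesses. The difference and SDs come from one earlier study at nine months post-stroke, while the primary endpoint is at twelve. Uncertainty in those inputs probably matters more than 3 patients per arm.

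All of this stands as to consequence: the real trial may well have more than 80% power. It does not make the sentence right. The sample size section claims no gain from covariates or from partial follow-up, and the article gives no correlation from which to claim one. Nor is this a detail left to a fuller document, since every figure involved is printed in the section. The point is that those figures disagree with one another.

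**Conclusion.** The concern holds. The 55 per arm is correct for the stated inputs, but 66 per arm does not preserve it under the stated 20% drop-out. The target falls short by 3 per arm (6 in total), and unadjusted power is about 78 to 79% instead of 80%.

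This rests on the protocol's own basis: an unadjusted two-sample comparison of those with a 12-month score, with drop-out read as a fraction of those recruited. It does not show that the adjusted analysis will be underpowered. The error is certain and minor in effect, but it makes the stated sample size wrong as written, so it should be corrected.

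**What to change.** Correct the sentence on drop-out in one of three ways:

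- **Keep 132 and restate what it covers.** Say that 66 per arm retains 55 for drop-out of up to 16.7%, or that it gives about 78% power (two-sample t-test, unadjusted) at 20% drop-out. This costs one sentence and no patients.
- **Correct the inflation.** State 55/0.8, rounded up to 69 per arm and 138 in total. This costs 6 more patients.
- **Keep 132 and justify it.** Give an explicit assumed correlation between discharge and 12-month GDS-15, with its source, and show the power of the adjusted analysis at 20% drop-out. This costs a short addition and no patients.

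The first option is enough to make the section internally consistent.

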### Statistical methods

The primary outcome measure for the participants who have had a stroke is the total score on the GDS-15 measured at 12 months post-stroke, with scores ranging from 0 to 15 (with 15 indicating more severe symptoms). The main independent variable is group, which comprises two levels: intervention and control. When considering group differences on the GDS-15 at 12 months, it is important to control for severity of disability (initial FIM-motor score), previous history of depression (yes/no), length of stay in hospital, and discharge GDS-15. Mixed regression models for repeated measures will be used to examine group differences over time on the GDS-15 controlling for these variables. These models will also be used to assess group differences on patient secondary outcomes, and group differences on carers' variables.

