Collaborative goal setting will be conducted at discharge by the treating inpatient rehabilitation team members using Goal Attainment Scaling (GAS) [34] for all participants. Inpatient rehabilitation staff will undergo training regarding goal setting principles and the application of GAS (inservice program, booklet, and competency questionnaire). Rehabilitation team members will specifically discuss with the patient (and carer, if available) what activities they participated in prior to their stroke and which of those activities could represent goals to be pursued in the first year post-stroke. The determination of relevant, new activities based on current activity status will also be considered. Goals can be set across the domains of body structure/function, activity status, and participation status, depending on the ability level of the individual. However, emphasis will be placed on setting goals that enhance home and community participation levels, and reflect valued activities according to the patients' preferences. Should the goals that are nominated by the patient be considered unrealistic by the rehabilitation team, efforts will be made to determine achievable, preliminary goals that provide the foundation for more complex goals. This will be done via discussions with the patient until a collaborative compromise is reached.

An assessor, who is blind to group allocation, will conduct interviews in the participants' place of residence at T2 (six months post-stroke) and T3 (twelve months post-stroke). The assessor will repeat the measures taken at T1 (GDS-15, MMSE, FIM-motor, SUPPH), and will also include the additional outcome measures of:

- participation, using the (1) the Activity Card Sort (ACS) [35,36] and (2) the London Handicap Scale (LHS) [37]. (1) The ACS aims to measure the impact of disability on participation status by quantifying the percentage level of retained and lost activities. Q-sort methodology is employed using photo cards that depict everyday activities over three occupational performance domains (household, social/educational, and leisure). The ACS-AUS (Recovery version) will be utilised in this study, which consists of 82 activities validated to the Australian population [36]. (2) The LHS aims to measure the level of participation restriction across the six dimensions of the WHO disability framework (mobility, physical independence, occupation, social integration, orientation, and financial self-sufficiency) 

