- health-related quality of life, using the Assessment of Quality of Life (AQoL) instrument [26]. The AQoL measures five dimensions of Health Related Quality of Life (HRQoL): illness, independent living, social relationships, physical senses, and psychological well-being. The tool consists of 15 items, each with four response levels. The AQoL has shown to be sensitive to changes in health states, and Australian population norms are available [39].

There will also be documentation of which health and community services are utilised by the participants who have had a stroke at each assessment timepoint during the first year post-stroke.

The primary outcome measure for the participants with stroke is depressed mood, which will be assessed by the GDS-15. Secondary outcomes for the participants with stroke are: participation (ACS and LHS); HRQoL (AQoL), activity/functional status (FIM-motor); self-efficacy (SUPPH); and cognition (MMSE).

Carer outcomes will be collected at T2 and T3, which include the GDS-15, ACS, and AQoL, and the Zarit Burden Index (ZBI) [40]. The ZBI aims to measure carers' perception of their caring role, and the degree to which they feel burdened by that role. Twenty-two items are measured on a 5 point scale, and an overall burden score is formed (0 = no burden to 88 = severe burden). Concepts within the scale cover notions of personal life, social life, health, emotional well-being, and finances [40].

The Human Research Ethics Committees (HREC) of both St.Vincent's Hospital Melbourne and The University of Melbourne have granted approval for this project. Written informed consent will be required from patients and their informal carer. If a patient is unable to grant informed consent (for example, due to cognitive deficits, dysphasia, reduced level of alertness), then a 'person responsible' (as defined in HREC guidelines) is eligible to give consent.

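### The GDS-15 covariate set is carried to the patient secondary outcomes with no own-baseline adjustment named for SUPPH, MMSE and FIM-motor, although each has a pre-randomisation score

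*Protocol article*

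**What the plan says.** The Statistical methods section lists the covariates for the primary outcome: "it is important to control for severity of disability (initial FIM-motor score), previous history of depression (yes/no), length of stay in hospital, and discharge GDS-15". It then gives the model: "Mixed regression models for repeated measures will be used to examine group differences over time on the GDS-15 controlling for these variables". The next sentence extends it: "These models will also be used to assess group differences on patient secondary outcomes", and to the carer outcomes as well. No covariate specific to any secondary outcome is named.

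The Procedures section lists the patient secondary outcomes: "Secondary outcomes for the participants with stroke are: participation (ACS and LHS); HRQoL (AQoL), activity/functional status (FIM-motor); self-efficacy (SUPPH); and cognition (MMSE"). It also shows which of them have a baseline. The T1 assessment takes place at rehabilitation discharge, before randomisation, and covers MMSE, FIM-motor, GDS-15 and SUPPH. For six and twelve months the article says "The assessor will repeat the measures taken at T1 (GDS-15, MMSE, FIM-motor, SUPPH), and will also include the additional outcome measures of" participation (ACS and LHS) and quality of life (AQoL). Three of the six secondary outcomes therefore have a T1 score and three do not.

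The Randomisation section stratifies on the admission FIM-motor score. That is a separate measurement from the T1 FIM-motor score at discharge.

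**The concern.** For the primary outcome the authors treat its own discharge score as a covariate that matters. The same reasoning applies to SUPPH, MMSE and FIM-motor, where the own pre-randomisation score is usually among the stronger predictors of the later score. The text instead carries over discharge GDS-15, which measures mood. For SUPPH and MMSE, no covariate on the same scale is named. For FIM-motor the list contains the initial score, most naturally the admission score used for stratification, and not the discharge score taken just before allocation.

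What is at stake is the width of the confidence intervals for three secondary outcomes, and how far a chance difference between the arms at T1 carries through to the estimated effect. The primary analysis is not affected.

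**Working it through.** **1. Which outcomes are affected**

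| Secondary outcome | T1 score collected | Same-scale covariate named |
|---|---|---|
| SUPPH | yes | none |
| MMSE | yes | none |
| FIM-motor | yes | initial score only |
| ACS, LHS, AQoL | no | not possible |

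**2. The plan's own figure.** The Power and sample size section gives a difference of 1.4, an SD of 2.6, two-sided alpha of 0.05 and 80% power. The formula n = 2(1.960 + 0.842)² × 2.6² / 1.4² gives 54.1, rounded up to 55 per arm, so the stated 55 is reproduced. This figure concerns the GDS-15 only; the article states no power for any secondary outcome. Recruiting 66 per arm with 20% loss leaves 66 × 0.8 = 52.8, about 53 per arm, which is used below.

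**3. Assumptions.** The documents give no correlations. Let q = 0.3 be the correlation of a secondary outcome with discharge GDS-15, and r its correlation with its own T1 score, varied from 0.3 to 0.8.

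**4. Residual variance and detectable difference.** As a fraction of the outcome variance, the residual is 1 − q² = 0.91 with discharge GDS-15 and 1 − r² with the own T1 score. The difference detectable with 80% power, in SD units, is (1.960 + 0.842) × √(2 × residual / 53) = 0.544 × √residual.

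| Adjustment | Residual variance | Detectable difference (SD) | 0.91 / residual |
|---|---|---|---|
| None | 1.00 | 0.54 | – |
| Discharge GDS-15, q = 0.3 | 0.91 | 0.52 | 1.00 |
| Own T1, r = 0.3 | 0.91 | 0.52 | 1.00 |
| Own T1, r = 0.5 | 0.75 | 0.47 | 1.21 |
| Own T1, r = 0.6 | 0.64 | 0.44 | 1.42 |
| Own T1, r = 0.7 | 0.51 | 0.39 | 1.78 |
| Own T1, r = 0.8 | 0.36 | 0.33 | 2.53 |

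The last column is the factor by which the sample would have to grow to give the same precision without the own T1 score.

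**5. Adding rather than replacing.** Suppose both scores are in the model and correlate 0.3 with each other. The residual is then 1 − (r² + q² − 2rq × 0.3) / (1 − 0.3²). This gives 0.86, 0.73, 0.62, 0.50 and 0.36 for r = 0.3, 0.5, 0.6, 0.7 and 0.8. Keeping discharge GDS-15 alongside the own T1 score changes little when r is high and gives a small gain when r is low.

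**6. Chance imbalance.** With 53 per arm, the between-arm difference in a T1 score has a standard error of √(2/53) = 0.19 SD. Left unadjusted, an imbalance of that size shifts the later estimate by about r × 0.19, for example 0.12 SD at r = 0.6.

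**The case against.** The strongest reply is that the text does not say the T1 values go unused. A repeated-measures model of group differences over time could take T1 as a response occasion for SUPPH, MMSE and FIM-motor, and the outcome's own baseline would then inform the comparison. This stands as a possibility, so a reader who infers that the plan discards the T1 scores goes further than the article allows. The article nevertheless points the other way. Discharge GDS-15 is a covariate in the primary model, which makes six and twelve months the natural response occasions. ACS, LHS, AQoL and all carer outcomes are collected only at those two times, so this is also the only structure common to all outcomes.

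A second reply is that the extension refers to the class of model, with the matching baseline substituted. In its favour, the same sentence covers carers, who have no discharge scores of their own. That shows the wording is loose, but the models just described are the ones controlling for the listed variables, and nothing states a substitution.

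A third reply is that covariates for each outcome belong in a full analysis plan, which is not shown and could settle the matter. Silence alone would indeed be no fault. Here, however, the article names a covariate set and applies it to outcomes for which it was not chosen.

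Four stronger readings are tempting and are not supported:

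- The point does not reach all six secondary outcomes. Three have no T1 score, and FIM-motor is partly adjusted already.
- It does not imply bias. T1 precedes randomisation, so only precision and chance imbalance are at issue.
- A gain equivalent to about 2.7 times the sample needs the two most favourable assumptions together: 0.96 / 0.36 = 2.67, with correlations of 0.2 and 0.8. It also gives no credit for the other listed covariates.
- The change is not free of cost. The Participants section accepts that patients with cognitive or communication deficits may not complete every assessment, so T1 SUPPH or MMSE may be missing for some.

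**Conclusion.** The point holds as a limited one. Read as written, the plan adjusts three secondary outcomes for discharge GDS-15 and names no adjustment for their own T1 score; for FIM-motor the gap is partial. If the own-T1 correlation is 0.5 to 0.8 and the correlation with discharge GDS-15 is 0.3, the residual variance is about 18% to 60% lower with the own score (0.75/0.91 to 0.36/0.91), and the detectable difference falls from about 0.52 SD to 0.47–0.33 SD. If the own-T1 correlation is near 0.3 there is little or no gain. These correlations are assumptions, and the calculation leaves out the other listed covariates, so the gain for FIM-motor in particular will be smaller than the table shows. The primary analysis and its sample size do not depend on this point. It is worth correcting because the data are already collected and the choice should be fixed before unblinding.

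**What to change.** State the covariates by outcome. For SUPPH, MMSE and FIM-motor, do one of the following and say which:

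- add the outcome's own T1 score to the listed covariates and specify how a missing T1 score is handled; or
- model T1 as a response occasion, with baseline means constrained equal across the two groups, which also keeps patients whose T1 score is missing.

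For FIM-motor, also say whether the initial score means the admission score. Leave the model for ACS, LHS and AQoL unchanged, since they have no T1 value. The cost is a sentence or two in the analysis section and no new data collection. The one real burden is the missing-baseline rule needed under the first option.
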